**Methods:**

This prospective, single-center observational cohort study is embedded within the Rheumatoid Arthritis DMARD Tapering (ROADMAP) clinic at Freeman Hospital, Newcastle upon Tyne, United Kingdom. Adults with clinician-confirmed RA in remission who are undergoing or are about to begin DMARD tapering will be recruited, with a target sample of 100 participants. Participants will be followed for 12 months, with clinical assessments aligned with routine ROADMAP visits at baseline and approximately months 3, 6, 9, and 12 together with ad hoc visits for suspected flare. Continuous wrist-worn accelerometry and weekly RA-FQ responses will be collected throughout follow-up. Clinical assessments will include tender and swollen joint counts, patient and physician visual analog scales, C-reactive protein, the DAS28-CRP, and Health Assessment Questionnaire Disability Index scores. The primary outcome is time to first clinically confirmed flare, defined as DAS28-CRP≥2.4 and/or at least 1 swollen joint attributable to inflammatory RA activity. Dynamic risk prediction methods, such as landmarking models, will use longitudinal accelerometry-derived physical activity, mobility, gait, and sleep measures to estimate flare risk over prespecified prediction horizons. Model performance will be assessed using time-dependent discrimination, calibration, predictive values, and lead time before clinically confirmed flare.

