**Inclusion criteria**
Clinical diagnosis of rheumatoid arthritis (RA) made by a consultant rheumatologist28-joint Disease Activity Score with C-reactive protein (DAS28-CRP)<2.4 at point of enrollment to the studyCurrent (or expected within the next 28 days) tapering of a disease-modifying antirheumatic drug (DMARD; conventional synthetic, targeted synthetic, or biologic)Able to walk at least 4 m independently without walking aidsPatient willing to commit to complete remote Rheumatoid Arthritis Flare Questionnaire (RA-FQ) and continuously wear monitoring devices

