#### Extension Study: Months 6, 9, and 12 Visits (±1 Week)—If Participating in Optional Extension Study

Participants entering the optional extension may attend follow-up visits at month 6 (week 24 ±1 wk), month 9 (week 36 ±1 wk), and month 12 (week 52 ±1 wk). At the month 6 and month 9 visits, participants will verbally confirm their willingness to continue. Changes in concurrent medications and any AEs since the previous visit will be recorded at each visit. A researcher will assess the 28-joint tender and swollen joint counts and the patient and physician visual analog scales. CRP results obtained through routine clinical care will also be recorded to calculate the DAS28-CRP. Participants will complete the HAQ-DI and a paper RA-FQ unless they have completed the online RA-FQ within the preceding 24 hours.

A clinically confirmed flare will be defined as a DAS28-CRP of ≥2.4 and/or at least 1 swollen joint attributable to inflammatory RA activity. Confirmed flares will be managed by the ROADMAP clinical team as part of routine care, and the study investigator will record the estimated date of flare onset. At each visit, completed paper questionnaires and Axivity AX6 devices from the preceding monitoring period will be collected. Participants who do not wish to continue at month 6 or month 9 will complete the wearable usability and acceptability questionnaire and exit the study. All participants remaining in the study at month 12 will complete the questionnaire and exit the study. No participant will be followed for more than 12 months from baseline. These optional extension visits will be implemented only after approval of the submitted ethics amendment and all required sponsor and site approvals.

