If arthritis flare is confirmed, defined as a DAS28-CRP of at least 2.4 or at least 1 swollen joint, this will already have been treated appropriately during the concurrent ROADMAP clinic appointment. The study investigator will record the estimated date of flare onset, and follow-up in the main study period will be terminated if not already completed. Patients who are not already enrolled in the optional 12-week extension study will be offered enrollment. If they agree, they will immediately enter the extension phase, any paper questionnaires and Axivity AX6 devices from the last visit will be collected, and they will be provided with 3 new Axivity AX6 devices and 1 wrist strap to wear for 28 days each in sequence on the nondominant wrist, or the dominant wrist if needed. If they cannot access the online REDCap portal, they will also be given 12 additional paper RA-FQs to complete weekly, and their next study visit will take place in 12 weeks according to schedule 6.3, replacing the planned week 12 main study visit. If the patient is already enrolled in the optional extension study, they will be given a feedback questionnaire on AX6 usability and acceptability, will continue wearing the AX6 monitors and completing any provided paper RA-FQs for the remainder of the ongoing 12-week extension period, and will then exit the study without an extension week 12 review to avoid an extra visit outside the ROADMAP clinic schedule; they will also be given a stamped addressed envelope to return the AX6 monitors and paper questionnaires by post. If a patient with confirmed flare declines the optional extension study, they will exit the study at that visit, any paper questionnaires and AX6 devices from the last visit will be collected, and they will be given a feedback questionnaire on AX6 usability and acceptability together with a stamped addressed envelope for postal return to the study team. If arthritis flare is not confirmed, the patient will continue to wear the Axivity AX6 monitors and complete RA-FQs according to the current schedule and will attend the next study visit as already arranged.

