### Clinical Discretion

It is possible for DAS28-CRP scores to be elevated by events unrelated to inflammatory arthritis: for example, by a concurrent infection causing an elevation of CRP, or trauma causing a painful or swollen joint. The study investigator has discretion to discount such false elevations of the DAS28-CRP and follow the remission section for the relevant study visit if felt to be appropriate. In such cases, it is expected that the study investigator’s decision should match that of the ROADMAP service clinician; for example, if a patient with concurrent infection had an elevated DAS28-CRP, but the ROADMAP clinician considered their arthritis to still be in remission, then the study investigator should manage the patient as being in remission.

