### Primary Analyses

The primary outcome is the time from study enrollment to the first clinically confirmed RA flare, defined as a DAS28-CRP of 2.4 or above.

The primary objective of the study is to predict clinically confirmed flare risk using dynamic risk prediction methods based on daily accelerometry data including both the quality metrics and the physical activity measures. In addition, we would like to retrospectively assess the accuracy of the model vs patient-reported flare.

We will use landmarking models to develop a dynamic risk prediction approach for arthritis flare. Landmarking is a time-updated survival modeling framework that generates risk predictions at predefined time points (landmark times) using information available up to each time point. Predictions are then made over specified future time horizons.

The approach consists of two components:

A longitudinal submodel, which summarizes repeated accelerometry-derived measurements over timeA time-to-event submodel, which estimates the risk of flare from each landmark time

At each landmark time, the longitudinal submodel is used to extract summary measures of the accelerometry data up to that time, and these summaries are then included as predictors in the time-to-event model to estimate the future risk of flare.

The event of interest is the first clinically confirmed arthritis flare. Participants who do not experience a clinically confirmed flare will be censored at the end of their individual follow-up period or at earlier withdrawal.

For the time-to-event component, we will fit both Cox proportional hazards models and random survival forests (RSFs) to assess potential improvements in predictive performance and capture potential nonlinear relationships and interactions. We also consider including variables such as age, sex, Clinical Frailty Score, and anticitrullinated protein antibodies (ACPAs) antibody status (either positive/negative or the actual titer) as fixed effects or variables in both longitudinal and time-to-event submodels as they are clinically important.

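### The primary event is DAS28-CRP ≥2.4 alone in Primary Analyses, but DAS28-CRP ≥2.4 and/or an RA-attributable swollen joint in the Abstract and Extension Study sections

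*Protocol article*

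**What the plan says.** Two places define the primary outcome event:

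- Primary Analyses: "first clinically confirmed RA flare, defined as a DAS28-CRP of 2.4 or above", with no swollen-joint limb.
- Abstract, Methods: "defined as DAS28-CRP≥2.4 and/or at least 1 swollen joint attributable to inflammatory RA activity".

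The visit sections define a confirmed flare as follows:

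- Extension Study (months 6, 9 and 12): "A clinically confirmed flare will be defined as a DAS28-CRP of ≥2.4 and/or at least 1 swollen joint attributable to inflammatory RA activity".
- Month 3 Visit and Ad Hoc Flare Visits: "If arthritis flare is confirmed, defined as a DAS28-CRP of at least 2.4 or at least 1 swollen joint", without the attribution wording.

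Four other provisions bear on the point:

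- At an ad hoc visit with confirmed flare, "follow-up in the main study period will be terminated if not already completed". Patients not yet in the optional extension are then offered it.
- Clinical Discretion: "The study investigator has discretion to discount such false elevations of the DAS28-CRP". Its examples are infection, and trauma to a joint.
- Primary Analyses censors anyone without a clinically confirmed flare when their own follow-up ends or when they withdraw.
- The disease-activity entry criterion in Textbox 2 is "with C-reactive protein (DAS28-CRP)<2.4 at point of enrollment to the" study. No listed criterion concerns swollen joints.

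**The concern.** The event definition decides who counts as a flare, on what date, and who is censored. Every label used to fit and test the prediction model follows from it. Two incompatible definitions of the same primary outcome are in print, and only one matches the rule by which flares are confirmed at visits. A patient who meets the swollen-joint limb alone is a flare for study conduct and a non-flare for the analysis described in Primary Analyses. With both definitions available and the main analysis run only after follow-up is complete, the choice could also be made after the results are seen.

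**Working it through.** **1. The conflict.** This step needs no arithmetic. The Abstract and Primary Analyses name the same outcome. One has a swollen-joint limb and the other does not. The and/or wording itself presupposes that a swollen joint can occur with DAS28-CRP below 2.4; otherwise that limb would add nothing.

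**2. A patient with a swollen RA joint and DAS28-CRP <2.4, if Primary Analyses governs.** By the visit sections this is a confirmed flare, managed by the clinic; the Introduction says treatment then returns to the previously effective dose. In the analysis there is no event, and what follows depends on the route:

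- Ad hoc visit, extension declined: the patient exits at that visit and is censored there. The exit is triggered by the flare, so the censoring is informative.
- Ad hoc visit, extension accepted: follow-up continues for 12 weeks and the patient stays at risk after treatment has changed.
- Ad hoc visit, already in the extension: monitoring runs to the end of that period, then the patient exits without a final review, event-free unless DAS28-CRP later reaches 2.4.
- Flare at month 3, 6 or 9: a flare does not by itself end follow-up. Those who continue stay at risk; those who leave are censored.

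For patients who stay, the 14-day windows covering the flare are labelled event-free. If DAS28-CRP later reaches 2.4, the event takes the later date.

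**3. Baseline, if the composite governs.** Textbox 2 tests only DAS28-CRP. The withdrawal rule in Delay to Final DAS28-CRP Calculation also refers only to that score. A patient with a swollen RA joint and a score below 2.4 can therefore enrol and already meet the composite on day 0.

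**4. The plan's figure, and sensitivity to the definition.** Inputs from Target Recruitment Sample Size: AUC 0.8 against 0.6, flare rate 50%, two-sided 0.025, 90% power, N = 100. The Hanley-McNeil variance is [A(1−A) + (n₁−1)(Q₁−A²) + (n₀−1)(Q₂−A²)]/(n₁n₀), with Q₁ = A/(2−A) and Q₂ = 2A²/(1+A). With 50 flares and 50 non-flares:

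- SE at 0.6 = √(8.01/2500) = 0.0566; SE at 0.8 = √(4.951/2500) = 0.0445.
- Power = Φ[(0.2 − 2.241 × 0.0566)/0.0445] = Φ(1.64) = 0.95.
- N for 90% power is 85, or 89 with the Obuchowski binormal variance.

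The stated 100 is not reproduced exactly. It matches if an unstated loss of 10% to 15% is added (85/0.85 = 100; 89/0.90 = 99).

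Now let s be the share of composite flares that are swollen-joint-only, and suppose the 50% refers to the composite. Both are assumptions. The DAS28-only rate is then 0.5(1−s). If the omitted flares also score like other flares but are labelled non-flares, the observable AUC is (50 × 0.8 + 50s × 0.5)/(50 + 50s).

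| s | DAS28-only events per 100 | Power, AUC still 0.80 | AUC with mislabelling | Power with mislabelling |
|---|---|---|---|---|
| 0% | 50 | 95% | 0.80 | 95% |
| 10% | 45 | 94% | 0.77 | 82% |
| 30% | 35 | 90% | 0.73 | 47% |
| 50% | 25 | 80% | 0.70 | 21% |

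If instead the 50% describes DAS28-only events, Primary Analyses keeps 50 events and the composite gives 50/(1−s): 56 at s = 10% and 71 at s = 30%.

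**The case against.** Several points on the other side stand.

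- A reader might count three definitions, because the Month 3 and Ad Hoc sections drop the attribution wording. Clinical Discretion names trauma as a cause of a swollen joint and lets the investigator follow the remission pathway, so it largely covers that gap. Nor need Primary Analyses repeat the discretion rule, since it speaks of clinically confirmed flare. The substantive conflict is between two definitions.
- A reader might infer that every swollen-joint-only flare is censored at the moment of flare. The text does not say so. The termination clause ends only the main period, applies only at ad hoc visits, and is followed by the extension offer. Censoring at the flare visit affects those who leave then, chiefly by declining the extension.
- A reader might infer that prevalent flares will be counted as incident ones. Patients are referred and enrolled as being in clinician-judged remission, and the Abstract and Extension Study require the swelling to be attributable to RA. The listed criteria leave a gap, but its frequency is unknown.
- The harm can be repaired. Joint counts and the score's components are recorded at visits, so either endpoint can be derived. Only 16 patients had been recruited by 1 July 2026.

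None of this settles which definition governs the primary outcome.

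**Conclusion.** The contradiction is direct and rests on no assumption: the same primary outcome has two definitions, and study conduct follows the one that Primary Analyses omits. If Primary Analyses is the operative text, treated flares are mislabelled and censoring at flare-triggered exit is informative. If the composite is operative, the entry criteria leave a smaller gap at day 0.

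The size cannot be given. The table's values of s are illustrations, and its last two columns need the further assumption that swollen-joint-only flares look like other flares on accelerometry. It would be wrong to infer that the study is underpowered: losing events alone leaves about 90% power at s = 30%, and the document supports no particular s. The case for correction is that the primary endpoint is ambiguous and the remedy is cheap.

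**What to change.** - Reconcile the passages to one statistical endpoint, worded identically in the Abstract and Primary Analyses and fixed before analysis. The composite, with the attribution clause and the Clinical Discretion rule, is the definition consistent with how follow-up is run.
- Report DAS28-CRP ≥2.4 alone as a sensitivity analysis.
- In Target Recruitment Sample Size, and in Ethical Considerations where the rate is introduced, state which definition the 50% refers to.
- As a secondary matter, use the baseline joint count already collected to state that patients who meet the event definition at baseline are not in the analysis risk set, or exclude them in a sensitivity analysis. An endpoint based on newly swollen joints is not proposed, because the baseline section describes counts and not which joints are swollen.

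The cost is wording, one sensitivity analysis (a second if baseline cases are handled that way) and possibly a few patients leaving the risk set. No new data are needed, and no change to the clinical handling of flare is proposed.

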### Target Recruitment Sample Size

This is explicitly a development project phase, and as such the analysis is intended to produce pilot data to support and inform the design of a future larger definitive trial of remote monitoring in DMARD tapering. To determine the required sample size for the current study, our primary focus lies in testing whether the area under the curve (AUC) derived from the risk prediction model is significantly greater than a cut-point of 0.6. Assuming a true AUC of 0.8 and flare rate of 50%, we will be able to reject the null hypothesis (H0: AUC ≤0.6) with 90% power and a 2-sided type I error rate of 0.025 with a target recruitment size of 100 patients.

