### Study Visits

#### Baseline Visit

Following the completion of the ROADMAP, patients attend baseline study visit (day 0). Patients attending their initial appointment will first undergo the inclusion and exclusion criteria check (Textbox 2).

Once the inclusion and exclusion criteria check is complete, patients will undergo the following study procedures in sequence. First, all patients will have the opportunity to discuss the study further with a study investigator before signing the consent form. Patients will next provide baseline information, including age, sex, address, telephone number, email address, past medical history, Clinical Frailty Score, Charlson Comorbidity Index, current medications, smoking status, and alcohol intake, after which height and weight will be recorded [16,17]. For each DMARD, the drug name and class, route, current dose and dosing frequency, reference therapeutic dose, proportion of the reference dose at enrollment, date and magnitude of the most recent dose reduction, number of previous tapering steps, and planned next tapering step will also be recorded. A researcher will then examine the patient to document the 28-joint tender and swollen counts, patient visual analog scale, and physician visual analog scale required for 28-joint Disease Activity Score with C-reactive protein (DAS28-CRP) disease activity assessment, and CRP blood test results obtained as part of routine clinical care during the ROADMAP clinic visit will also be recorded for DAS28-CRP calculation (Multimedia Appendix 2) [5,18].

Textbox 2.Inclusion and exclusion criteria for study participation.

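### If clinical covariates enter the primary model, passing the test of whole-model AUC above 0.6 would not show that accelerometry predicts flare, because no planned comparison isolates it

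*Protocol article*

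**What the plan says.** The Introduction gives the main objective as showing that accelerometry monitoring is feasible and accurate for detecting flare during tapering. Primary Analyses frames the primary objective as flare prediction from daily accelerometry data.

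Four statements bear on whether the plan can deliver that:

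- **Test.** Target Recruitment Sample Size puts the primary focus on "testing whether the area under the curve (AUC) derived from the risk prediction model is significantly greater than a cut-point of 0.6", "with 90% power and a 2-sided type I error rate of 0.025" and "with a target recruitment size of 100 patients", assuming a true AUC of 0.8 and a flare rate of 50%.
- **Model content.** Primary Analyses adds: "We also consider including variables such as age, sex, Clinical Frailty Score", and ACPA status or titer. These would enter "as fixed effects or variables in both longitudinal and time-to-event submodels as they are clinically important". The decision is left open.
- **Label.** Textbox 1 (secondary subobjectives) and Secondary Analyses call the comparator for the combined RA-FQ model the accelerometry-only model.
- **Comparisons.** Three model comparisons are planned: Cox against random survival forest, clinically confirmed against patient-reported flare as the outcome, and accelerometry plus RA-FQ against the accelerometry-only model.

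Other performance measures are listed. The Abstract names calibration, predictive values and lead time; Primary Analyses adds sensitivity, specificity and kappa against patient-reported flare; Strength and Limitations repeats AUC, sensitivity, specificity and predictive values. None has a pass mark or a reference model.

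**The concern.** The time-to-event submodel produces the risk that is scored. Any covariate placed there can raise the AUC directly, whether or not the accelerometry summaries carry information. The hypothesis concerns the AUC of the model as a whole, so rejecting it says that something in the model discriminates, not which part.

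The plan applies added-value reasoning to the RA-FQ by comparing models with and without it. It does not do so for the device that the study exists to evaluate. The comparison across flare definitions cannot fill the gap: the same covariates could make both models perform well, yet Secondary Analyses would read that result as evidence that the accelerometry signals are robust.

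At stake is the pilot's main message. A later multicenter study could be designed around an AUC that age, sex, frailty and antibody status had largely supplied.

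**Working it through.** **1. Does any planned comparison isolate accelerometry?**

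| Planned comparison | What differs | Accelerometry removed? |
|---|---|---|
| Cox vs random survival forest | Fitting method | No |
| Clinically confirmed vs patient-reported flare as outcome | Outcome | No |
| Accelerometry + RA-FQ vs accelerometry-only | RA-FQ | No |

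None does. The accelerometry-only label would be accurate only if the optional covariates were left out.

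**2. Inputs.** From the sample size section: null AUC 0.6, true AUC 0.8, flare rate 50% (so 50 flares and 50 non-flares), two-sided level 0.025 (z = 2.2414), N = 100. Assumed, because the protocol gives no such figure: true AUC of the covariates alone of 0.60, 0.65, 0.70 or 0.75, with accelerometry adding nothing.

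**3. Formula.** One-sample AUC z-test with Hanley-McNeil variance:

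Var(A) = [A(1−A) + (n1−1)(Q1−A²) + (n0−1)(Q2−A²)] / (n1·n0), with Q1 = A/(2−A) and Q2 = 2A²/(1+A).

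P(pass) = Φ[(A − 0.6 − z·SE(0.6)) / SE(A)].

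**4. The plan's own figure.** SE(0.6) = √0.003204 = 0.0566 and SE(0.8) = √0.001980 = 0.0445. Power at N = 100 is Φ[(0.20 − 2.2414 × 0.0566)/0.0445] = Φ(1.643) = 95.0%. This method needs 85 patients for 90% power; the Obuchowski binormal variance needs 89. With the variance taken at the alternative instead, the two methods need 62 and 75. The stated 100 is not reproduced exactly but errs on the safe side, and would be consistent with an unstated loss of about 10–15% (89/0.90 = 99; 85/0.85 = 100). The point here does not depend on it.

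**5. Passing without any contribution from accelerometry.** The observed AUC that passes is 0.6 + 2.2414 × 0.0566 = 0.727.

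| Covariates-only true AUC | SE | (A − 0.727)/SE | P(pass) |
|---|---|---|---|
| 0.60 | 0.0566 | −2.24 | 1.2% |
| 0.65 | 0.0548 | −1.40 | 8% |
| 0.70 | 0.0522 | −0.51 | 30% |
| 0.75 | 0.0488 | 0.47 | 68% |

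Across Hanley-McNeil and Obuchowski variances, each evaluated at the null or at the alternative, the last three rows range over 8–9%, 30–37% and 68–80%. The table shows the low end.

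**6. How precisely could the difference be estimated?** Full-model AUC 0.80, N = 100, 50 flares, two-sided 0.025. The correlation r between the two AUCs is assumed to be 0.3, 0.5 or 0.7. SE(diff) = √(V1 + V0 − 2r√(V1·V0)).

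| Covariates-only AUC | Power at r = 0.3 / 0.5 / 0.7 |
|---|---|
| 0.60 | 86% / 95% / >99% |
| 0.65 | 61% / 77% / 94% |
| 0.70 | 31% / 42% / 65% |
| 0.75 | 9% / 12% / 19% |

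For 0.70 against 0.80 at r = 0.5, the SE is 0.049, so a 95% interval would extend about ±0.10 around a true difference of 0.10.

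**7. Limit of these figures.** They use one binary outcome per patient. The planned predictions cover 14 days from weekly landmarks. If 50 flares were spread evenly over 12 months, about 50/26 ≈ 2 would fall in each 14-day window. Precision at a single landmark would be lower than shown.

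**The case against.** The strongest reply is that the harm depends on a step not yet taken. The covariates are only under consideration, the objective is worded in terms of accelerometry, and two places call the model accelerometry-only. If they are left out, no covariate can take the credit. That stands, and the point is conditional on it. But the text also permits the opposite choice, and the two descriptions cannot both hold once covariates are in.

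A reader might infer that the model is judged by AUC above 0.6 alone. The documents do not support that: several other measures are planned. AUC above 0.6 is the only criterion with a threshold, and none of the other measures separates accelerometry from covariates.

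A reader might also infer a fault in the absence of taper-stage variables and baseline DAS28-CRP from the named predictors. The covariate list is open-ended, and the taper details are recorded at baseline ("proportion of the reference dose at enrollment, date and magnitude of the most recent dose reduction, number of previous tapering steps"). Variables not named as predictors are not shown to inflate the planned AUC, so this is a preference about predictors and forms no part of the point.

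It can also be said that covariate lists and reference models belong in an analysis plan that is not shown. That would answer a complaint about missing detail. Here the article itself states the test, the candidate predictors and the comparisons, and those do not support the intended inference if covariates enter.

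Finally, this is declared a development phase producing pilot data, and a formal test of the difference would often miss a real contribution (31–65% power if covariates alone reach 0.70). That rules out making every accelerometry claim hang on the difference. It does not rule out reporting the difference as an estimate.

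**Conclusion.** The concern holds in conditional form. The protocol describes its primary model in two incompatible ways, ties its only thresholded criterion to the whole model, and plans no comparison that isolates accelerometry. If covariates enter, a pass would not show that accelerometry predicts flare. If they do not, misattribution to them does not arise.

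The size depends on how well the covariates discriminate alone, which the protocol does not say. The chance of passing with no contribution from accelerometry is negligible at a covariates-only AUC of 0.60 (about 1%) and material from about 0.70 (30%, rising to 68% at 0.75). These are illustrations under one outcome per patient and an even split of flares. They do not predict how the 14-day landmark analysis will behave. The logical gap does not depend on them.

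This should be settled before analysis. It changes what the study can conclude, and the remedy uses data already being collected.

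**What to change.** 1. State in Primary Analyses whether age, sex, Clinical Frailty Score and ACPA enter the primary model, and make Textbox 1 and Secondary Analyses agree. Reserve the accelerometry-only label for a model without them.
2. If they enter, also fit a reference model with the same covariates and no accelerometry, using the same Cox and random survival forest methods, weekly landmarks, 14-day horizon and resamples.
3. Report the AUC difference (covariates plus accelerometry minus covariates alone) with a participant-level bootstrap confidence interval. Present it as an estimate, not a pass/fail test, and word conclusions about accelerometry in light of it.

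The cost is one extra reference model per fitting method, with no new data, visits or participants. The downside is an imprecise difference at N = 100, which the report should say plainly. With 16 participants recruited by July 1, 2026 and the main analysis due only after all follow-up is complete, there is time to prespecify it.
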